### Outcomes

#### Primary outcome

The primary outcome, the Borderline Personality Features Scale for Children (BPFS-C) [76], is a 24-item dimensional measure adapted from the borderline scale of the Personality Assessment Inventory (PAI) [77] for use with children and adolescents from 9 years of age. It has the same four subscales as the PAI borderline scale: Negative Relationships, Affective Instability, Self-harm and Identity Problems. The 24 items are rated on a 5-point Likert scale, ranging from 1 (not at all true) to 5 (always true) with a higher total score indicating more severe levels of borderline personality features. Crick et al. [76] established evidence for the construct validity and demonstrated high internal consistency. Evidence for cross-informant concordance, criterion and concurrent validity were established by Sharp and colleagues [78]. Satisfactory construct and criterion validity has also been found for the abbreviated 11-item version of the BPFS-C [79]. In an RCT of individual MBT for adolescents [53], the BPFS-C was found to be sensitive to clinical change.

#### Secondary outcome measures

*Depression* will be measured with the Beck’s Depression Inventory for Youth (BDI-Y) from Becks Youth Inventories of emotional and social impairment, which have also proven valid and reliable in Danish [80].

*Self-harm* will be measured using the self-report scale on self-harm from the Risk-Taking and Self-Harm Inventory for adolescents (RTSHIA) [81]. The RTSHIA is a 38-item measure adapted from the adult Self-Harm Inventory [82] to be suitable for use with adolescents. The 38 items are rated on a 4-point Likert scale with higher scores indicating a higher frequency with which the adolescent has engaged in risk-taking or self-harming behaviors. The RTSHIA has been shown to have very high reliability (Cronbach’s alpha = 0.89, test–retest reliability = 0.93) and validity.

*Externalizing and internalizing symptoms* are measured by the Youth Self-Report (YSR) [83] and a corresponding parents’ version, the Child Behavior Checklist (CBCL) [84]. One hundred twelve items are rated on a 3-point scale with “0” for not true, “1” for somewhat or sometimes true, or “2” for very or often true. Both the internalizing and the externalizing scales comprise symptom scales corresponding to DSM diagnoses. A total problem score is derived by summing up all the symptom scales. The YSR and the CBCL are established evidence-based assessment instruments [85], which have also been validated and standardized in a Danish sample [86, 87].

*Borderline personality disorder symptoms* are measured with the Zanarini Rating Scale for Borderline Personality Disorder (ZAN-BPD) [88], which is a semi-structured interview with ratings from 0 (no symptoms) to 4 (severe symptoms) on each of nine items corresponding to the nine DSM-IV criteria for borderline personality disorder. ZAN-BPD has been used in previous studies of pharmacological and psychological treatments for people with BPD. It is reliable, sensitive to change, and has highly convergent validity with structured clinical ratings of BPD [89].

*Global assessment of functioning* will be assessed with the Children's Global Assessment Scale (C-GAS) that has shown validity in measuring functioning in children [90] and sufficient inter-rater reliability in a Danish sample [91].

*Parental reports.* In addition to the parents’ version of the YSR, the CBCL, described above, we will also collect parental reports on borderline personality features using the parents’ version of the BPFS-C, the BPFS-P [78].

*Sociodemographic information* will also be collected at baseline during assessment procedures and from medical records.

Furthermore, reduction in the number of patients’ hospital admissions and visits to the emergency room will be used as a secondary outcome measure. All patients included in the study will be followed in the National Health Register, and we will extract data from the register dating back to the date before the patients were enrolled in the study as well.

### Mediational variables

*Attachment* will be assessed with the Experience of Close Relationships Inventory (ECR) [92] and with the Inventory of Parent and Peer Attachment-Revised (IPPA-R) [93]. The ECR is a 36-item self-report questionnaire measuring attachment in romantic relationships. It has displayed good psychometric properties. The IPPA-R is a valid and reliable 53-item measure of attachment in adolescence. It comprises two scales that measure attachment to parents and peers, respectively.

*Mentalization* will be assessed with the 46-item measure Reflective Function Questionnaire for Youth (RFQ-Y) [94].

### Measurement intervals

The primary and all self-report-based secondary outcomes are measured at baseline, week 10, 20, 30, and after the 40^th^ and final MBT group session. Secondary outcomes based on interviews and expert ratings (the ZAN-BPD, C-GAS) are measured at baseline and discharge. The test-battery designed for intake, including basic clinical evaluation, mediational and outcome measures will take an estimated time of 6 hours per patient. Table 1 lists the primary and secondary outcomes, along with mediational measures.

**Table 1 Tab1:** Assessments administered at baseline and each follow-up point throughout the trial

Assessment points	Outcome and mediational self-report measures	Expert ratings and clinician-administered measures
Baseline	Patient: BPFS-C, YSR, BDI-Y RTSHIA, ECR-R, IPPA-R, RFQ-Y Parent: CBCL, BPFS-P	Patient: C-GAS, ZAN-BPD
10 weeks, 20 weeks, 30 weeks	Patient: BPFS-C, YSR, BDI-Y RTSHIA, ECR-R, IPPA-R, RFQ-Y Parent: CBCL, BPFS-P	
Discharge	Patient: BPFS-C, YSR, BDI-Y, RTSHIA, ECR-R, IPPA-R, RFQ-Y. Parent: CBCL, BPFS-P	Patient: C-GAS, ZAN-BPD

*BPFS-C* Borderline Personality Features Scale for Children, *YSR* Youth Self-Report, *BDI-Y* Becks Depression Inventory for Youth, *RTSHIA* Risk-Taking and Self-Harm Inventory for adolescents, *ECR-R* Experience of Close Relationships Inventory-Revised, *IPPA-R* Inventory of Parent and Peer Attachment–Revised, *RFQ-Y* Reflective Function Questionnaire for Youth, *C-GAS* Children's Global Assessment Scale, *ZAN-BPD* Zanarini Rating Scale for Borderline Personality Disorder

We will have weekly self-report-based assessment in relation to group sessions (40 measurements) and patients will fill out questionnaires in the beginning of each group session. The assessment comprises a short form of the BPFS-C, the BPFS-C-11, and the short version of the Youth Self-Report, the BPM-Y (19 items). This is to be able to monitor closely when in the treatment program possible progress, and development in the patients’ psychopathology is obtained.

All applied instruments will be applied in Danish translated versions. Published Danish versions exist of the SCID-II, the CBCL, the YSR, the BDI-Y, the ECR-R and the ZAN-BPD. The authors translated the remaining instruments.

### Deterioration

Any patient whose mental health deteriorates during treatment will be taken care of according to official guidelines and treatment recommendations in the Department. We will perform subgroup analyses of patients with an increased score on the primary outcome at discharge (i.e., after the 40th session), in order to enhance our knowledge about what characterizes patients who do not benefit or deteriorate from treatment [95].

### Sample size

Sample size is determined for the primary outcome, namely, the total score of the BPFS-C. A 12-point difference between the two treatment groups is considered to be clinically important. The only outcome study using the BPFS-C to date reported a standard deviation of outcome of 15.4 for psychotherapeutic treatment with a patient group similar to ours. With 90 % power and a two-tailed significance level of 5 %, 72 patients would need to be randomized to the two treatment arms. This calculation does not, however, take into account the similarity of patients who are treated by the same therapists and potential dropout.

Patients in the MBT group will be treated in five groups with two therapists in each group. These are slow open groups with six to seven patients, which will include a new patient as soon as another patient has finished treatment. Group treatments are known to cause similarity of the outcomes within groups, which needs to be accounted for in the sample size planning. We expect an intraclass correlation of 0.03, and a total number of eight patients treated in each of the groups, the design effect is 1.24. Thus, the sample size has to be increased by 24 % (which would be 90 patients). For simplicity, we assume the same intraclass correlation in the control group because the control patients are nested within therapists even if the treatment is individual.

Intention-to-treat (ITT) analysis will be used, as it is the recommended approach to evaluating RCTs ITT analysis includes every subject who is randomized according to randomized treatment assignment and it ignores noncompliance, protocol deviations, withdrawal, and anything that happens after randomization. Hence, ITT analysis preserves prognostic balance produced from the original random treatment allocation, but the treatment effect generated from ITT analysis is generally conservative. We will recruit 20 % more patients to have powerful tests in both the ITT as well as in the per protocol population even in the presence of dropout. This yields a total of 112 patients to be randomized, in a 1:1 ratio.

### Randomization, methods to minimize bias, and blinding

In order to keep assessors blind to the patients’ treatment allocation, all pretreatment assessments will be carried out prior to randomization. Randomization to either MBT or TAU are done online by the trial coordinator (the first author) using a stratified block randomization procedure with a computer-generated allocation sequence with a varying block size kept unknown to the investigators by Public Health and Quality Improvement Data Management*.* Stratification will be according to clinic affiliation and borderline severity, that is, scores on the BPFS-C. More stratification variables are relevant (i.e., socioeconomic status), but not possible to apply due to the small number of participants. Patients randomized to the MBT will initiate the individual case formulation sessions (see Fig. 1) prior to MBT-I, and thereby will initiate the treatment program immediately. Patients randomized to TAU are allocated to a therapist and begin individual sessions immediately.

Assessments during the treatment phase are limited to self-report measures, hence no blinding will be possible. All information given to the participants before completing the self-reports will be standardized.

Regarding outcome assessments at discharge, we will minimize bias that knowledge of treatment allocation could cause by implementing the following strategies: (a) outcome assessors will be blind to treatment allocation, (b) outcome assessors and therapists will not directly communicate with each other, and (c) patients are asked not to reveal their treatment allocation during outcome assessments. Furthermore, outcome assessors will be asked to guess the patients’ treatment allocation so that the effects of possible bias can be examined in the analysis and all outcome assessor interviews will be recorded and a random sample will be re-rated by independent raters. Outcome assessors will be research assistants or clinical psychologists, who have not been trained in MBT, have not been involved in delivering treatment to participating patients, and have not carried out any intake procedures, including baseline assessments. The statistician will perform statistical analyses with the two intervention groups coded as ‘A’ and ‘B’, with randomly chosen therapist identifications.

### Data management and statistical approach

Data-management will be handled by Public Health and Quality Improvement Data Management from Central Denmark Region, Aarhus. They will provide support with randomization, set up questionnaires electronically and will keep the data on their secure servers. Hence, none of the staff members involved in the study will have access to outcome data during the treatment phase.

All analyses will be conducted according to the ITT principle. Characteristics of the treatment groups will be described at baseline. Preliminary analysis will investigate the pattern of missingness at follow-up, and multiple imputation will be used for missing values. The primary outcome is the total score of the BPFS-C, which is treated as a continuous, normally distributed variable. The primary efficacy hypothesis will be tested using a multilevel two-group comparison (MBT vs. TAU), with Group as a main effect, Therapy Group as a random intercept (within the MBT group, see, e.g., [96]), the prerandomization BPFS-C as a continuous covariate and the stratification factor clinic as categorical covariate. The test will be performed at the 5 % two-tailed significance level. The primary test for efficacy will be based on the intention-to-treat population, with all randomized patients entering the analysis set, and multiple imputation of missing values. The result will be expressed as the covariate-adjusted difference in group averages, along with the two-sided 95 % confidence interval.

For the secondary outcomes, similar analyses will be used, taking into consideration the scale of the variable (e.g., logistic regression for binary outcomes). A sensitivity analysis will be based on the per protocol set for the available cases (without imputation). Linear regression and logistic regression analyses will be conducted to examine the predictive power of the different covariates (i.e., personality pathology, mentalizing, and attachment) on treatment efficacy and treatment completion.

We will use multiple imputations for missing values in the primary and secondary outcomes [97]. Separate imputation models will be used for the two treatment groups [98]. The imputation models will include the primary and secondary endpoints (baseline and follow-up) as well as the covariates of the primary statistical analysis, and therapist time in hours.

The primary analysis will be based on the pragmatic comparison of the two treatment arms and will, therefore, not take different amounts of therapist time within or across groups into account. To account for possible differences in therapist time, a sensitivity analysis will be performed on the change scores in which the obtained values will be divided by the actual patient-specific hours of therapist contact.

Mediation analyses will be carried out to test for potential mediating effects of both mentalizing and attachment. As recommended by Hayes [99], we will conduct structural equation analyses (SEM), using Preacher and Hayes [100] methods for estimating indirect and direct effects with multiple mediators. Unstable participation in the therapy is expected. A dropout will be determined by clinicians as ending therapy without agreement with the therapist.

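### The primary model clusters the MBT arm only, although the sample-size section treats TAU patients as clustered by therapist with the same ICC; under the plan's own assumptions the SE is modestly understated

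*Protocol article*

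**What the plan says.** **Planning (Protocol article, Sample size).** For the MBT arm: "We expect an intraclass correlation of 0.03, and a total number of eight patients treated in each of the groups", from which "the design effect is 1.24". For the TAU arm: "we assume the same intraclass correlation in the control group because the control patients are nested within therapists even if the treatment is individual". The inflation covers the whole sample: "Thus, the sample size has to be increased by 24 % (which would be 90 patients". A dropout allowance then brings the total to 112, randomized 1:1.

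**Analysis (Protocol article, Data management and statistical approach).** The primary test is a multilevel comparison of the two arms with "Therapy Group as a random intercept (within the MBT group, see, e.g., [96", together with "the prerandomization BPFS-C as a continuous covariate and the stratification factor clinic as categorical covariate". Missing values are multiply imputed. The sensitivity analyses concern the per-protocol set and therapist hours. None allows for clustering in the TAU arm, and no robust variance is mentioned.

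**Data available (Randomization, methods to minimize bias, and blinding).** Each TAU patient is allocated to a therapist. The statistician receives arms coded A and B "with randomly chosen therapist identifications".

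**The concern.** A random intercept in one arm is a recognised model for partially nested trials, but it is valid only if the patients in the other arm are independent. The Sample size section says they are not. Its appeal to simplicity covers only the choice of an equal ICC; the nesting of TAU patients within therapists is stated as fact.

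If outcomes are correlated among patients of the same TAU therapist, the variance of the TAU mean is larger than the planned model reports. The estimate is not biased, but the confidence interval would be too narrow and the test would reject a true null hypothesis more often than 5% of the time. This matters because it is the confirmatory test of the trial, and because the two sections cannot both describe the TAU arm correctly.

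**Working it through.** **Inputs.** From Sample size: difference 12 points, SD 15.4, two-sided 5%, power 90%, ICC 0.03, design effect 1.24, five MBT groups, 112 patients at 1:1 (56 per arm). The number of TAU patients per therapist is not given, so it is varied below as an assumption.

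**1. The plan's own figures.** The normal approximation gives 2 × (1.960 + 1.282)² × 15.4² / 12² = 34.6, or 35 per arm. The t-based calculation gives 36 per arm, 72 in total (power 90.3%). Then 72 × 1.24 = 89.28, rounded up to 90, and 89.28 / 0.8 = 111.6, rounded up to 112. The chain 72, 90, 112 reproduces.

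Eight patients per group at ICC 0.03 give 1 + 7 × 0.03 = 1.21; the stated 1.24 corresponds to nine patients. This hardly affects the present point (see step 3).

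**2. Standard error under each description of the TAU arm.** SE = SD × √[(DE_MBT + DE_TAU) / n per arm].

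- Clustering in MBT only (planned model): 15.4 × √[(1.24 + 1) / 56] = 3.08; CI half-width 1.96 × 3.08 = 6.04.
- Clustering in both arms (planning assumption): 15.4 × √[(1.24 + 1.24) / 56] = 3.24; half-width 6.35.
- Ratio: √(2.24 / 2.48) = 0.950, so the SE is about 5% too small.
- Actual two-sided error: 2 × [1 − Φ(1.96 × 0.950)] = about 6.3%; coverage about 93.7%.

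**3. Dependence on the TAU caseload.** DE_TAU = 1 + (m − 1) × 0.03, with DE_MBT = 1.24:

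| TAU patients per therapist (assumed) | SE too small by | Type I error |
|---|---|---|
| 1 | 0% | 5.0% |
| 3 | 1.3% | 5.3% |
| 5 | 2.6% | 5.6% |
| 8 | 4.4% | 6.1% |
| about 11 | 6.2% | 6.6% |
| 14 | 7.7% | 7.1% |

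With 1.21 in both arms (eight per cluster) the result is 4.4% and 6.1%.

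**4. With clinic in the model.** The formula ignores the clinic covariate, which absorbs part of the variation between therapists. A simulation of the REML mixed model (five MBT groups, four clinics, 56 per arm, ICC 0.03) gave these rejection rates under the null:

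| TAU caseload up to | Clinic in model | MBT intercept only | With TAU therapist intercept |
|---|---|---|---|
| 8 | yes | 5.8% | 5.4% |
| 11 | yes | 5.7% | 5.1% |
| 11 | no | 6.3% | 5.3% |

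The first two rows rest on 8,000 runs each (Monte Carlo standard error √(0.05 × 0.95 / 8000) = 0.24 percentage points at 5%). With clinic included, the part due to the missing TAU term is about 0.4 to 0.6 percentage points. In those two rows the average SE was not below the empirical SD (ratio about 1.04), because variance estimates from only five groups, truncated at zero, tend to enlarge the SE.

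**5. Power once both arms are clustered.** With DE 1.24 in both arms, power is 91.3% at N = 90 and 95.9% at N = 112.

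**The case against.** The strongest reply is that the effect is small and its size uncertain. The 6.3% comes from a formula without the clinic covariate. With clinic included, the simulated rate is 5.7-5.8%, and a little of that excess remains even with a TAU intercept. TAU is delivered at four clinics by several professions, so caseloads may be small and the effect close to nil. The equal ICC is a planning convenience, conservative for sample size, and does not measure clustering in the TAU arm. In points, the half-width changes by about 0.3 against a target difference of 12. All of this stands and limits the size of the finding. It does not remove the contradiction, since the protocol gives no reason for treating TAU patients as independent in the analysis.

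A reader might infer three stronger points, which the document does not support:

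- **That a large-sample Wald test on five groups adds further optimism.** The protocol names no test statistic, estimator or degrees-of-freedom method. Such details commonly belong to the statistical analysis plan, which is not shown.
- **That the blinded analysis is lost.** A random effect in one arm does require knowing which code is MBT, but the model can be run under both codings, or data management can supply the cluster variable. At most this deserves a note.
- **That the error is large.** Rates well above 7% need an ICC higher than the plan's 0.03 or caseloads above 14 patients per therapist, and the protocol states neither.

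**Conclusion.** The inconsistency is real: the sample size treats both arms as clustered, and the primary model clusters one. Under the plan's own assumptions (ICC 0.03, design effect 1.24 in both arms, SD 15.4, 56 per arm) the SE is up to about 5% too small and type I error up to about 6.3%. The direction requires only that the TAU ICC is above zero and that at least some TAU therapists treat more than one trial patient. The protocol assumes the first, and its nesting statement implies the second. The magnitude rests on an unstated caseload and is smaller with clinic in the model, at about 5.7-5.8%. It is a modest flaw in the primary test. It biases neither the estimate nor the power calculation, and it is worth correcting because the correction is cheap.

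**What to change.** In the primary model, add a random intercept for treating therapist in the TAU arm alongside the one for therapy group in the MBT arm. Give the two arms separate variance components. Name a small-sample degrees-of-freedom method (for example Satterthwaite or Kenward-Roger) and say how it combines with the pooling over imputed data sets, for instance as the complete-data degrees of freedom in the Barnard-Rubin adjustment. Assign patients who never start treatment to the group or therapist intended for them, so that every randomized patient has a cluster. State the expected number of TAU patients per therapist. Note how the model will be run under the A/B coding.

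If the sponsor prefers to keep the one-arm random intercept, the weaker alternative is to justify independence in the TAU arm and report the two-arm model as a sensitivity analysis.

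The cost is a slightly wider interval, about 0.3 points in half-width at the plan's design effect, and some care with variance components estimated from few clusters. Coded therapist identifiers already appear to be in the analysis data. The sample size need not change.

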**Discussion:**

This is the first randomized controlled trial to test the efficacy of a group-based mentalization-based treatment for adolescents with BPD or subthreshold BPD. If the results confirm our hypothesis, this trial will add to the treatment options of cost-effective treatment of adolescent BPD.

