### Experimental intervention: MBT in groups

Mentalization-based group therapy is constituted by a set of treatment principles. Naturally, some principles overlaps with individual MBT (i.e., “regulating arousal” and “keeping an affect focus”), but others are specific to the group component (i.e., identifying and mentalizing events in the group) [62, 67]. The patients’ profound difficulties with interpersonal functioning and affect regulation require therapeutic techniques potent enough to counteract the difficulties that can arise during sessions. A main therapeutic goal is to balance the management of therapist authority and structure of each session with the open-minded, exploring, and curious stance in order “to create and sustain a mentalizing discourse in the group” [62, 67].

MBT in groups is a 1-year psychotherapy program with three components, MBT-Introduction (MBT-I), MBT-Group (MBT-G) and MBT-Parents (MBT-P).

MBT-I is a structured 3-week introductory psychoeducative program for patients covering the concepts of mentalizing and attachment, and information about BPD. MBT-I includes role plays and discussions of cases and video clips in order to encourage active participation. Furthermore, the group members will be encouraged to participate in small homework assignments between the sessions. MBT-I was developed by [name] and [name] [66], and modified for our purpose in collaboration with the authors.

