Mentalization-based group therapy (MBT-G) consists of 37 weekly sessions of mentalization-based psychotherapy in groups. Sessions are not accompanied by continuing individual sessions. However, case formulations are made with patients during individual sessions with both therapists, and this process scaffolds and supports the therapeutic work in the group. The overall purpose of the case formulation sessions is for therapists and patient to develop a clear mutual understanding of the patient’s main difficulties and psychotherapeutic focus points, which can be drawn on during group sessions. The case formulation is to be formulated within the mentalization-based framework, applying the theoretical understandings and principles from mentalization theory. The individual focus in these sessions organizes thinking for therapists and patient and supports the mentalizing work in the ensuing group sessions [62]. Three individual case formulation sessions are scheduled before the initiation of the MBT-G. The patient will also be informed which therapist is his or her contact person, and an updated crisis plan with the therapist’s contact details is included in the formulation. After eight to ten group sessions and again toward the end of the program (after 25 group sessions), a case formulation session is scheduled for revising the formulation according to the deepened knowledge and development of the patient.

MBT-P is a psychoeducation program for the patients’ parents running parallel to MBT-I and MBT-G. It is a slow-open six-session program comprising role plays, plenary analysis of difficult interpersonal events between parent and adolescent and therapists’ presentations with information on BPD, mentalization, and attachment. The importance of parents’ continuous support of their adolescents’ attendance to treatment is also discussed. All sessions have a length of 90 minutes. MBT-P is adapted from [name] and [name]’s manual [66]. An overview of the entire MBT in groups program is presented in Fig. 1. Both MBT-P as well as the contact-person function mentioned above are intended to prevent premature dropout of the treatment.

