### Treatment as usual

TAU is based on supportive techniques and comprises psychoeducation, counseling and, if needed, ad hoc crisis management with the overall aim of alleviating BPD symptomatology. TAU is delivered by child and adolescent mental health professionals with thorough experience in working with psychopathology in adolescents. They will be psychologists, psychiatrists, social workers or nurses employed in child and adolescent psychiatric clinics in Region Zealand. Adherence to the supportive approach is monitored in regular supervision, as TAU is not manualized. For the purpose of this study, we defined a limit for the minimum treatment by standardizing to *at least* 12 individual monthly sessions. Additional contact may vary across clinics and according to the needs of the patient. The supervisors and staff selected to carry out the TAU treatment and supervision have no previous MBT training. They will not be undertaking MBT training during the trial, nor will they deliver MBT to patients in- or outside the trial. We will monitor and register both the MBT and TAU patients’ contact to the health system during the treatment period, to be able to report both quantitatively and qualitatively the treatment both groups have received.

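### Dividing each patient's change score by therapist hours does not adjust the treatment effect for therapist time, and can turn a true MBT benefit into an apparent TAU advantage

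*Protocol article*

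**What the plan says.** All points are from the protocol article. Under Data management and statistical approach, the primary analysis is a pragmatic intention-to-treat comparison that will "not take different amounts of therapist time within or across groups into account". The text then adds a sensitivity analysis meant to allow for unequal hours, which is to be carried out "on the change scores in which the obtained values will be divided by the actual patient-specific hours of therapist contact". No model or test is named for this analysis, and contact hours are not defined for a patient treated in a group.

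The planned contact differs by arm:

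- **MBT** (Experimental intervention: MBT in groups): "MBT-I is a structured 3-week introductory psychoeducative program", and MBT-G "consists of 37 weekly sessions of mentalization-based psychotherapy in groups", which makes 3 + 37 = 40 weekly sessions. Three individual case-formulation sessions come first and two revisions follow. The same section says "All sessions have a length of 90 minutes", but in the paragraph on the parents' programme.
- **TAU** (Treatment as usual): a minimum of "12 individual monthly sessions", with further contact according to need, no upper limit and no stated session length.

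The Discussion acknowledges that treatment dose may be unequal because MBT is weekly.

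**The concern.** A sensitivity analysis should ask the primary question again under different assumptions. Dividing by hours asks a different one: how many BPFS-C points were gained per hour. It works as an adjustment for time only if a patient with no contact would not change at all and every further hour adds the same amount. That is hard to defend here. Entry requires a BPFS-C total above 67, so some regression to the mean is likely in both arms whatever the contact. That shared improvement would be divided by a much larger number in MBT.

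Three further problems follow from the ratio itself:

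- It is undefined at zero hours and extreme for patients who leave early, although the protocol expects unstable participation and analyses all randomised patients.
- The denominator arises after randomisation, and in TAU it depends on the patient's needs.
- The result is in points per hour, so it cannot be set beside the primary estimate in BPFS-C points.

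At stake is the reading of the trial. Under the label of sensitivity analysis, a reversed sign would be taken as evidence that a positive primary result is not robust.

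**Working it through.** **The plan's own figures.** The protocol gives no figure for the per-hour analysis. Its sample size inputs, reused below, are a 12-point difference, SD 15.4, two-sided 5% and 90% power. A noncentral t calculation gives 36 per arm, or 72, as stated. Then 72 × 1.24 = 89.3, stated as 90, and 89.28/0.8 = 111.6, stated as 112, or 56 per arm.

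**Session counts alone.** MBT 40 + 5 = 45, TAU 12. 45/12 = 3.75, so MBT needs 3.75 times the TAU improvement to tie.

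**Break-even.** Let c be the mean TAU improvement, c + 12 the mean MBT improvement, and Hm and Ht the hours. With the same attendance pattern in both arms, the order reverses when

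(c + 12)/Hm < c/Ht, that is, c > 12 × Ht/(Hm − Ht).

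Assumed MBT hours: 40 × 1.5 h + 5 × 1 h = 65 h. The 90 minutes is carried over from the parents' paragraph, and one hour per case-formulation session is an assumption. TAU session length is not given, so Ht is varied.

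| TAU hours | Break-even TAU improvement |
|---|---|
| 12 | 144/53 = 2.7 points |
| 20 | 240/45 = 5.3 points |
| 24 | 288/41 = 7.0 points |
| 30 | 360/35 = 10.3 points |

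Example at 12 TAU hours with c = 12: MBT 24/65 = 0.37 and TAU 12/12 = 1.00 point per hour.

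**How often the reversal is significant.** Simulation settings, all assumptions except the 56 per arm: change normal with SD 15.4 (the protocol gives this as an SD of outcome), change independent of hours, hours = full hours × Beta(3, 1.2), unadjusted two-sample test on change divided by hours. True MBT benefit is 12 points in this table.

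| MBT h | TAU h | TAU improvement | Significant for TAU |
|---|---|---|---|
| 65 | 12 | 12 | about 87% |
| 65 | 20 | 12 | about 41% |
| 65 | 24 | 12 | about 18% |
| 65 | 30 | 12 | about 4% |
| 45 (60-minute sessions) | 12 | 12 | about 60% |
| 65 | 12 | 8 | about 43% |
| 65 | 12 | 5 | about 11% |

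If TAU does not improve at all, TAU is not favoured, but at 65 against 12 hours the ratio finds the 12-point MBT benefit in only about 17% of trials.

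**No true difference.** With 15 points of improvement in both arms, TAU is declared better in over 99% of trials at 12 TAU hours, falling to 84% at 30.

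**If group time is apportioned.** Two therapists shared among 8 to 6.5 patients: 60 × 2/8 = 15 h and 60 × 2/6.5 = 18.5 h. Adding five 1-hour sessions gives 20 to 23.5 h. Against 12 TAU hours the break-even rises to 144/8 = 18 and 144/11.5 = 12.5 points. Significant reversal at 24 against 12 points is then about 0 to 2%.

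**The case against.** The strongest reply is that little depends on this analysis. The primary test, estimate, interval and sample size do not use it, and no decision is attached to it. That stands, and it limits the severity.

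The reversal also rests on inputs the protocol does not give: TAU hours, mean improvement, the SD of change, the test, and whether hours are those attended or a share of therapist time. That stands too. The risk runs from near zero to near certain across plausible inputs, so reversal is a possibility and not a consequence built into the design.

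A reader might go further in three ways that the document does not support:

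- **That the baseline-adjusted model is abandoned.** The text fixes only the outcome (change divided by hours). It is silent on covariates and the random intercept.
- **That this is the only use made of therapist input.** Contact will be registered and reported for both arms, therapist hours enter the imputation model, and admissions and emergency visits are a secondary outcome.
- **That the cost-effectiveness claim rests on this ratio.** The abstract's statement that "this trial will add to the treatment options of cost-effective treatment of adolescent BPD" is conditional on the hypothesis being confirmed and is not linked to the per-hour analysis.

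None of this rescues the ratio for its stated purpose. Under equal improvement and hours attended it favours TAU in most trials, so it says nothing about robustness.

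**Conclusion.** The concern holds in limited form and should be fixed. The planned ratio measures improvement per contact hour and does not adjust the treatment difference for therapist time. This follows from the stated method and needs no simulation.

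That it can reverse a true 12-point MBT benefit depends on three conditions: hours mean hours attended, MBT patients attend more hours than TAU patients, and TAU patients improve on average. Under the simulation assumptions, with 65 MBT hours and a 12-point TAU improvement, significant reversal ranges from about 87% at 12 TAU hours to 4% at 30. With apportioned group time it is about 0 to 2%. It would be too strong to say that the analysis must favour TAU, or that the trial's main conclusion is compromised.

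**What to change.** Remove the per-patient ratio as a sensitivity analysis of efficacy. Keep the undivided, baseline-adjusted BPFS-C difference and report therapist hours by arm next to it.

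If a per-hour measure is wanted, compute it at arm level: adjusted BPFS-C difference divided by the difference in mean therapist hours, with a bootstrap interval. State whether group time is apportioned. Label it an efficiency measure that is not evidence on the robustness of the primary result. It becomes unstable if mean hours turn out similar in the two arms, in which case hours and effect should simply be shown side by side.

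Randomisation should not be used as an instrument for hours. The arms also differ in content, modality and parent programme, so allocation does not act through hours alone.

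The cost is a change of wording, best made before unblinding. No new data are needed, because contact is already registered. The downside is that a per-hour comparison is no longer available as a robustness check.
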